### Sample size calculations

Sample size calculations were based on the ability to detect a difference in service uptake through the Endline Household Survey. As noted earlier, only 26.5% of Malawian women had been screened at least once in their lifetime as of 2015 with use of VIA for primary screening [3], which is much lower than the targeted rate of 80% set at the onset of Malawi’s Cervical Cancer Control Program in 2004 [16]. We estimated that with the introduction of HPV self-sampling in our clinic-only arm, at least 40–50% of eligible women in our facility catchment areas will be screened during our 18 months of implementation. We then estimated that with the addition of HPV self-sampling in the community to reach rural women, we would be able to approach Malawi’s targeted rate of 80% of eligible women screened in our clinic + community arm. Based on data obtained from potential facilities in Lilongwe and Zomba, we also estimated an average cluster size of 8000 eligible women per health facility and a coefficient of variation of the cluster sizes of 0.35. Finally, we estimated that our intra-cluster correlation coefficient (ICC) will be between 0.12 and 0.19, based on other similar studies performed in Malawi, where the ICC ranged from 0.004 to 0.20 [25, 26]. With 16 randomized facilities (8 per arm), we initially estimated that we would have at least 80% power to detect a difference of at least 25–30% between our 2 arms, even if the proportion of women screened in the clinic-only arm is as low as 40%. For example, if the clinic-only arm found that 40% of women had been screened, we would have 80% power to detect a difference if the clinic + community arm had screened at least 75% of women in their catchment areas.

However, after performing site selection and randomization, we learned that the two central/district hospitals selected could not be assigned to model 2 as their HSAs did not perform community-based services. Therefore, we dropped these 2 hospitals from our sample size calculations and decreased our average cluster size to 3400 eligible women accordingly. With an ICC of 0.15 and coefficient of variation of cluster sizes of 0.35, we will have at least 83% power to detect of difference of at least 30% between our 2 arms (with 7 facilities in each arm), even if the proportion of women screened in the clinic-only arm is as low as 40%. All power calculations were calculated in R (Version 3.5.1, clusterPower package).

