#### Endline Household Survey

The Endline Household Survey, conducted at months 13–15 after implementation, will be the primary tool to assess the uptake of CCSPT and FP services among women in the catchment areas of the health facilities. Households will be sampled in a two-stage sampling design. Stage 1 will include a random sample of enumeration areas (EAs) from all of the facilities’ catchment areas. This random sample will be selected with the number of EAs proportional to the size of the catchment area. In each selected EA, we will undertake a household listing to create a sampling frame of households for the survey. In stage 2, a random sample of households will be selected. Our target sample size is up to 8000 women aged 15–50 years from the 16 health facility catchment areas. The age range is intended to include women most likely to utilize FP services, as well as those in the target range for CCSPT. With the expectation of ~1.1 women aged 15–50 in our households, the sample will include ~8000 households selected from 266 EAs selected proportionally from facility catchment areas (randomly selecting ~30 households/EA). Parental consent will be obtained for participants 15–17 years old, as described in the “Ethical considerations” section. If a randomly sampled woman does not consent for the survey, she will be replaced with another randomly selected woman from her EA.

Women aged 15–50 years will be eligible to participate in the interviewer-administered survey, provided that they have not had their cervix removed. The survey will cover demographic information, reproductive health information, HIV status, distance to the nearest health facility, prior FP use, FP use during project implementation, prior CCSPT services received, and CCSPT services received during project implementation.

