### Analysis plan

#### Endline Household Survey

Key outcomes from the Endline Household Survey include (1) the proportion of eligible women who have received CCS during the 18 months of study implementation, (2) the proportion of treatment-eligible women who received thermal ablation during the study period, and (3) the proportion of women aged 15–50 years who are using a modern FP method. These proportions will be calculated using descriptive statistics. Differences between the clinic-only and clinic-and-community models will be assessed via logistic regression, adjusted for district, facility size, and facility type. The regression model will account for health facility clustering, and analyses will be adjusted for the small number of clusters [28, 29].

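### The stated power of at least 83% makes no allowance for few clusters; a two-sided 5% small-cluster test on 14 facilities has about 75%

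*Protocol article*

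**What the plan says.** The section Sample size calculations gives the power after the two central/district hospitals were dropped: "we will have at least 83% power to detect of difference of at least 30% between our 2 arms". The claim refers to seven facilities per arm and a clinic-only screening proportion of 40%. The inputs are an ICC of 0.15, a coefficient of variation of cluster sizes of 0.35, and a mean cluster size that was reduced for the two lost hospitals: "decreased our average cluster size to 3400 eligible women accordingly". On method it says only "All power calculations were calculated in R (Version 3.5.1, clusterPower package". Alpha, sidedness, variance form and reference distribution are not given, and no allowance for few clusters is mentioned.

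The Analysis plan, under Endline Household Survey, describes a logistic regression "adjusted for district, facility size, and facility type". On the few clusters it then commits to a correction: "The regression model will account for health facility clustering, and analyses will be adjusted for the small number of clusters". The correction itself is left to two cited sources.

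Under Assessments, the survey is to interview only a sample of each catchment: "Our target sample size is up to 8000 women", spread over 16 catchment areas.

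**The concern.** With 14 facilities, a test that is valid for few clusters uses a critical value clearly above 1.96. If the power was computed with 1.96, the power statement and the analysis describe different tests, and the stated floor is higher than the planned test can deliver at the stated inputs.

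This is the primary comparison, and the results are meant to inform national policy. A reader who takes 83% at face value could read a non-significant result as stronger evidence against a 30-point benefit than the design supports.

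**Working it through.** **Inputs** (Sample size calculations): k = 7 facilities per arm, n = 3400, ICC = 0.15, CV = 0.35, p1 = 0.40, p2 = 0.70. Assumed: two-sided alpha of 0.05, because none is stated.

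**Step 1: reproduce the stated figure.**
- Design effect = 1 + [(1 + CV²)n − 1] × ICC = 1 + (1.1225 × 3400 − 1) × 0.15 = 573.3.
- Effective sample per arm = 7 × 3400 / 573.3 = 41.5.
- SE = √[(0.40 × 0.60 + 0.70 × 0.30) × 573.3 / 23,800] = 0.1041.
- 0.30 / 0.1041 = 2.881.
- Normal reference: Φ(2.881 − 1.960) = 82.2%, about one point from 83%.

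Other two-sided normal versions give 78.4% (pooled variance with the CV), and 86.3% (unpooled) or 82.9% (pooled) if cluster-size variation is ignored.

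**Step 2: same standardised difference, t reference on between-facility degrees of freedom.**
- 14 − 2 = 12 df, critical value 2.179: noncentral-t power 75.3%.
- 14 − 2 − 4 = 8 df, critical value 2.306: 71.4%. The 4 df are district 1, facility size 1 (one term) and facility type 2 (three types remain once the central/district hospitals are out). This takes the covariates to explain none of the between-facility variance.

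No two-sided t version reaches 83%. The highest is 80.0% (12 df, unpooled), and it ignores the loss from unequal cluster sizes.

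**Step 3: detectable difference at 80% power, from 40%.** 31.6 points on 12 df; 32.9 points on 8 df.

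**Step 4: what informative covariates would do.** Cutting the between-facility component by 25% (0.15 × 0.75 = 0.1125 in the design effect) gives a design effect of 430.2, SE 0.0902, a standardised difference of 3.33, and 82.9% on 8 df.

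**Step 5: the protocol's own ICC range, 40% v 70%.**

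| ICC | Normal | t, 12 df | t, 8 df |
|---|---|---|---|
| 0.12 | 89.6% | 84.0% | 80.5% |
| 0.15 | 82.2% | 75.3% | 71.4% |
| 0.19 | 72.6% | 65.3% | 61.3% |

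**Step 6: women interviewed instead of women eligible.** An even split is 8000 / 16 = 500 per facility: 75.0% on 12 df. If the sample follows catchment size, the 14 facilities hold about 14 × 3400 = 47,600 of the originally estimated 16 × 8000 = 128,000 women. That is 8000 × 47,600 / 128,000 = 2975 interviews, or about 212 per facility: 74.4% on 12 df. Either way the loss is under 1 point. (The survey covers ages 15–50 and screening eligibility ages 25–49, so the number contributing to the screening outcome would be smaller still.)

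**The case against.** **The method is inferred.** The article does not say that 1.96 was used, and the evidence is mixed. For the initial design (8 per arm, 8000 women, ICC 0.12, 40% v 65%) the normal formula gives 80.4%, which fits the claim of at least 80% at the lower end of the 25–30 point range; t on 14 df gives 74.5%. But the worked example of 40% v 75% at 80% power does not fit: the normal formula gives 90.6% to 98.5% over ICC 0.19 to 0.12, while a pooled t test on 14 df at ICC 0.19 gives 81.3%. This stands. The normal critical value is the best reading of the 83%, not a documented fact.

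**A one-sided test would rescue the figure.** Both effectiveness hypotheses are directional, and a one-sided 5% t test on 12 df gives 82.7% (pooled) to 85.7% (unpooled). This stands as a condition. The article nowhere claims one-sided testing, so the conventional two-sided 5% is assumed here.

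**The 71% is pessimistic.** Facility type is the randomisation stratum and may well explain some variance, and the df rule of the correction is not named. This also stands. A reader might infer that the planned analysis simply has 71% power; the documents do not support that, because they say nothing of how much variance the covariates explain.

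**The consequence is limited.** The protocol expects the community arm to approach 80% against 40–50% in the clinic-only arm. On t with 12 and 8 df, power is 96% and 94% for 40% v 80%, and 90% and 87% for 45% v 80%. At 50% v 80%, again a 30-point difference, it is 79% and 75%. A reader might therefore infer that the trial is underpowered for its expected effect and needs more facilities; the figures do not show that over most of the expected range. Nor do they show an inflated type I error, because the analysis plan commits to a small-cluster correction.

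**Conclusion.** The concern holds as a misstated figure. At the article's own inputs and a two-sided 5% level, the small-cluster test it plans has about 75% power for 40% v 70%, roughly 8 points below the stated floor of 83%.

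This rests on three assumptions: two-sided 5%; a t-type reference on between-facility degrees of freedom as the small-cluster correction; and, for the 75%, no net covariate effect in either direction. The 8-df result is a lower sensitivity value and not the headline. The use of eligible rather than interviewed women as the cluster size is a real mismatch but almost immaterial. The error lies in the reported power; the design and the planned test stand.

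**What to change.** In Sample size calculations, replace the claim of at least 83% with the power of the planned small-cluster test, and state alpha, sidedness and reference distribution. At two-sided 5%, report:

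- about 75% for 40% v 70% at ICC 0.15 (t, 12 df, before any covariate effect), or equivalently 80% power for a difference of about 31.6 points;
- about 71% as the lower sensitivity value (8 df, uninformative covariates; 80% power at about 33 points), noting that covariates explaining roughly 25% of between-facility variance would restore about 83%;
- about 84% at ICC 0.12 and 65% at ICC 0.19, both on 12 df.

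Use the expected number of women interviewed per facility as the cluster size. If a one-sided 5% test was intended, say so and give the power on that basis.

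The cost is one reworded paragraph and a less favourable figure. No facility is added and the analysis stays as planned.

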### Site selection and randomization

In each district, we selected 8 facilities that were representative of the 4 facility types in which our models would most likely be implemented: (1) one central/district hospital, (2) one CHAM hospital, (3) two urban health centers, and (4) four rural health centers. The facilities were chosen in consultation with the District Health Management teams of each district. We evaluated the readiness of each facility to implement our models, excluding those with no existing FP services or laboratories. We discussed potential facilities with other local partners, including other research groups, nonprofits, and international health organizations.

Once the 16 facilities were selected, they were assigned a code. The facilities were then randomized to one of the models in a 1:1 randomization within each of the 4 facility type strata (Table 3) by a UNC Project-Malawi biostatistician, using the facility codes. This randomization resulted in 8 health facilities assigned to model 1 (4 in Lilongwe, 4 in Zomba) and 8 health facilities assigned to model 2 (4 in Lilongwe, 4 in Zomba). However, when we discovered that neither Bwaila District Hospital in Lilongwe nor Zomba Central Hospital in Zomba could be randomized to model 2 given their lack of HSAs (see sample size text above), we determined that we could not include Zomba Central Hospital or Bwaila District Hospital in our analyses to compare model 1 and model 2 (see “Sample size calculations” section). Therefore, we will only be analyzing 14 health facilities for that comparison: 7 assigned to model 1 (3 in Lilongwe, 4 in Zomba) and 7 assigned to model 2 (4 in Lilongwe, 3 in Zomba).

**Table 3 Tab3:** Selected sites with their initially assigned model number, within their health facility stratum

Health facility strata	Lilongwe district	Assigned model	Zomba district	Assigned model
**Central/district hospital**	Bwaila District Hospital	1	Zomba Central Hospital	2^a^
**CHAM hospital**	Nkhoma Hospital	2	St. Luke’s Hospital	1
**Urban health center**	Kawale Health Center	2	Matawale Health Center	2
	Area 18 Health Center	1	Zomba City Clinic	1
**Rural health facility**	Kabudula Rural Hospital	1	Domasi Rural Hospital	2
	Lumbadzi Health Center	2	Namasalima Health Center	1
	Chileka Health Center	2	Ngwelero Health Center	1
	Chiwamba Health Center	1	Likangala Health Center	2

*CHAM* Christian Association of Malawi

^a^Bwaila District and Zomba Central Hospitals will not be included in the final comparison of randomized arms as these hospitals did not have health surveillance assistants who could provide community-based services for model 2

### Facility preparation

To facilitate facilities’ ability to deliver CCSPT services per our algorithm, we will conduct needs assessments at each selected site and organize procurements and facility rehabilitation. We will modify existing MoH registers for facility CCSPT, facility FP, and community FP services to capture information on the new services. In partnership with MoH, we will design new registers for HPV lab testing and community cervical cancer screening. We will organize technical training and project-specific training sessions for clinic providers, HSAs, and laboratory staff. These will cover how to give instructions for self-sampling (for both providers and HSAs), how to perform thermal ablation (for providers only), and how to conduct GeneXpert HPV testing (laboratory staff), as well as project-specific procedures for documentation.

### Description of models

In both model 1 and model 2, through group educational talks and one-on-one counseling, women will be educated about cervical cancer screening and the opportunity to perform self-sampling for HPV testing. The facility staff will be encouraged to hold the CCSPT educational talks in waiting rooms for the FP clinic, antiretroviral therapy (ART) clinic, and other clinics.

Once a woman presents to the CCSPT clinic at the facility, she will be offered self-collection if she meets the following eligibility criteria: (1) aged 25–49 years old, (2) no history of total hysterectomy, (3) no history of cervical cancer, and (4) not currently pregnant. Self-collected samples will then be sent to the facility laboratory for high-risk HPV (hrHPV) testing using the GeneXpert® (Cepheid Inc, Sunnyvale, CA, USA) platform. We chose to use the Xpert HPV assay because it offers several advantages over other commercially available HPV assays: results are available within 1–2 h, all reagents are contained in one cartridge, and laboratory personnel only need a short training course to use the machines. In addition, the Xpert HPV assay has been validated in Malawi, and many facilities in Malawi have already invested in Xpert machines for tuberculosis diagnostic testing [27].

Women who screen positive for hrHPV at the clinic will be offered same-day VIA to determine whether they are eligible for ablative treatment. Eligibility for thermal ablation requires that (1) no cervical lesions or any visible lesion covers <75% of the cervix and can be seen in its entirety, (2) the lesion does not extend into the endocervical canal or to the vaginal wall, (3) the squamocolumnar junction is visible, (4) the client is more than 3 months postpartum if recently pregnant, (5) there is no suspicion of cervical cancer, (6) there are no polyps or scarring impeding contact of the probe, and (7) there is no evidence of current menstruation or cervicitis. HPV-positive and treatment-eligible women will be offered thermal ablation on the same day of screening.

In model 2, women living in the health facility’s catchment area will also be offered self-sampling in the community. HSAs and other health facility staff will give educational talks about self-sampling to groups of women at village and outreach clinics. Interested women can perform self-sampling on the day of the community clinic, and HSAs will transport the sample back to the health facility for testing. Women can receive results at the next community clinic or by presenting to the associated health facility. If any women screens HPV-positive, she will be referred for VIA and possible treatment. Patient flow is illustrated in Fig. 2, with light blue shading for the community-based components.

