Introducing a screen-and-treat strategy that combines these innovations—self-sampling, rapid HPV assays, and thermal ablation—promises to improve screening and treatment rates in resource-limited settings including Malawi. However, success requires considering key implementation questions around how to target healthy women and how to reach rural women who have poor access to health facilities. Integrating cervical cancer screening with family planning (FP) services is a promising strategy because many women who access FP services are in the appropriate screening age range and sexually-active. Existing structures to deliver community-based FP services can be utilized to reach women in rural and isolated areas. Any solution for increasing CCSPT services in sub-Saharan Africa must be applicable to rural populations, since an estimated 60–75% of women who develop cervical cancer in sub-Saharan Africa live in rural areas [14].

In many countries, community health workers provide a vital link between health facilities and rural populations. Community-based FP services have been effective in increasing FP uptake in many countries [15], including in Malawi where 80% of the population is rural [16, 17]. Community health workers in Malawi, known as health surveillance assistants (HSAs), provide FP services to rural women through outreach and village clinics. Experience from other countries suggests that community health workers like HSAs can be successfully trained to offer self-sampling for HPV screening in rural areas [18, 19]. However, providing community-based screening introduces additional challenges for follow-up given that same-day screening and treatment will not be conducted. Understanding the impact of community-based screening on loss to follow-up is important given that one of the primary shortcomings in Malawi’s CCSPT program has been the low rate of treatment among screen-positive women. Thermal ablation may be more scalable than cryoablation but would only improve access if women are successfully informed of their results and linked to care at facilities.

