Service utilization data	De-identified information about CCSPT and FP services will be collected from clinic, HSA, and lab registers on a monthly basis.	Providers routinely record visit information in registers; research team members collect data	N/A (difficult to estimate projected number of clients for each register type)
Time and motion study	Research assistants will continuously observe providers, e.g., nurses and HSAs record the time spent on health care activities such as CCSPT and FP including non-health care activities	Providers, nurses, clinicians, HSAs, and lab staff	At least 1 staff member per facility from each category (e.g. provider, HSA, lab staff).
Client Exit Survey	This survey asks clients about the money and time expended accessing CCSPT and FP services at the clinics. It also includes the EQ-5D-3L survey to assess health-related quality-of-life for the cost impact analyses.	Facility clients	Up to 2370 participants (790 participants each at 3 time points, with the number of participants interviewed per facility proportional to the number of FP clients at that facility)

Throughout the implementation period, we will conduct weekly clinical supportive supervision visits and mentor the health facility providers, ensure appropriate logistical support, and assess providers’ fidelity to our protocols. Of note, while our study is ongoing, we will not restrict concomitant care or interventions at the study sites. Specifically, facilities are permitted to continue offering VIA and cryotherapy.

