**Fig. 2 Fig2:**
[figure not shown]
Patient flow for screening and treatment. Blue boxes and darker arrows indicate the community components that will only be present in model 2. *Note that result return will be delayed for community-screened women; same-day results will only be possible for women screened at facilities. HSA, health surveillance assistant

Educational talks and self-sampling instructions can be given by HSAs, nurses, mid-level providers, and doctors, while only nurses, mid-level providers, and doctors can perform VIA and thermal ablation. All clinical staff will undergo protocol-specific training sessions before conducting duties related to the new interventions. They will also receive weekly visits from the study’s clinical mentors (either clinicians or nurses), who will observe the clinical staff using observation checklists and collect data from the clinic and HSA registers on a monthly basis to promote adherence to study protocols and accurate data entry into the registers.

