Studies in other low-resource countries have demonstrated that training community health workers like HSAs to offer self-sampling is feasible and has the potential to improve screening coverage. In addition, the WHO now recommends self-testing options for sexual and reproductive health, including HPV self-sampling for primary cervical cancer screening [4]. A cluster randomized study in Argentina demonstrated a four-fold increase in screening rates with community health workers offering HPV self-sampling, compared with community health workers counseling women to undergo clinician-sampling at a facility [18]. In Uganda, screening was higher with community-based HPV self-sampling compared to the control of clinic-based VIA screening, in preliminary results from a cluster randomized trial [19]. The same project showed that community-based HPV self-sampling was more cost-effective than clinic-based VIA screening, with a wide margin for increasing costs of the HPV-based program [35]. Our study will investigate the feasibility of community self-sampling in Malawi and provide a direct comparison to facility-only services. Using stratified randomization further allows us to assess implementation success in a variety of settings, including urban and rural, district-level and local, and public and private facilities.

Linking community-screened women with appropriate care is crucial for cervical cancer prevention and can be especially challenging with community-based screening. In the pilot results of a Uganda trial comparing community HPV screening versus clinic-based VIA screening, over 50% of 73 women who were positive for hrHPV after community self-sampling could not be reached by telephone for result delivery [19]. Loss to follow-up is already a concern with the current standard of care in Malawi: only 43% of women who are VIA-positive receive appropriate treatment [3]. Our study will provide insight into whether appropriate follow-up is feasible with community-based screening.

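### The only follow-up outcome, survey-reported ablation among treatment-eligible women, omits HPV-positive women who never received their result, and no outcome or analysis uses the monthly registers to count them

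*Protocol article*

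**What the plan says.** All references are to the protocol article.

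- **The question.** The Background says "Understanding the impact of community-based screening on loss to follow-up is important". The Discussion cites a Ugandan pilot in which "over 50% of 73 women who were positive for hrHPV after community self-sampling could not be reached by telephone for result delivery", and then promises: "Our study will provide insight into whether appropriate follow-up is feasible with community-based screening".
- **Result return in model 2.** Under Description of models, "Women can receive results at the next community clinic or by presenting to the associated health facility". The Fig. 2 legend adds: "Note that result return will be delayed for community-screened women; same-day results will only be possible for women screened at facilities".
- **The measuring instrument.** "The Endline Household Survey, conducted at months 13–15 after implementation, will be the primary tool to assess the uptake of CCSPT and FP services". It is a single interviewer-administered survey. The Design section says that it will be used to compare screening and treatment rates between the models.
- **The outcome.** The Analysis plan lists three key survey outcomes: screening received, thermal ablation among treatment-eligible women, and modern FP use. Only the second concerns what happens after a positive test.
- **The registers.** Facility preparation says that "we will design new registers for HPV lab testing and community cervical cancer screening". Table 2 says that "De-identified information about CCSPT and FP services will be collected from clinic, HSA, and lab registers on a monthly basis", and places this row under Objective 3 (cost and budget impact). The Analysis plan names routine service utilization data only in micro-costing. Description of models gives a further use: clinical mentors collect clinic and HSA register data monthly to support protocol adherence and accurate entry.

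**The concern.** The step most at risk in model 2 lies between the laboratory and the woman. An HPV-positive woman who does not come back never has VIA, so nobody determines whether she could be ablated. Asked at endline, she can say that she gave a sample and heard nothing, but not that she was positive. The outcome on treatment therefore describes only women who got past the step in doubt.

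At a facility, results can be available the same day, so this loss should be small in model 1. The omission falls mainly on one arm and flatters it. The two models could show similar treatment proportions while differing in how many positives were ever told, and the trial could not say where the pathway fails. That is the follow-up question the article sets itself. The primary screening comparison is not touched, because a woman without a result can still report having been screened.

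**Working it through.** The article states no figure for follow-up, so there is none to reproduce. The check sets the sections side by side and then illustrates the size.

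**1. Who can enter the outcome.** Description of models uses VIA, after a positive HPV test, to decide eligibility for ablation, and refers community-screened positives to VIA. The outcome in the Analysis plan is restricted to treatment-eligible women. The order is: sample, test, result given, VIA, eligibility, ablation. A woman lost before the result is given has no eligibility status and is in neither numerator nor denominator. Read literally, a woman who was told but never attended VIA is also outside it.

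**2. Size (illustration).** Let u be the share of otherwise eligible positives never told their result, and t the share ablated among those told. The survey outcome shows t. The share among all otherwise eligible positives is (1 − u) × t. The overstatement is t − (1 − u)t = u × t. Both u and t are assumptions. The 50% is near the cited pilot's non-contact, and 43% is the article's national share of screen-positive women appropriately treated.

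| u | t shown by survey | (1 − u) × t | Overstatement (points) |
|---|---|---|---|
| 10% | 43% | 38.7% | 4.3 |
| 10% | 70% | 63.0% | 7.0 |
| 10% | 90% | 81.0% | 9.0 |
| 25% | 43% | 32.25% | 10.75 |
| 25% | 70% | 52.5% | 17.5 |
| 25% | 90% | 67.5% | 22.5 |
| 50% | 43% | 21.5% | 21.5 |
| 50% | 70% | 35.0% | 35.0 |
| 50% | 90% | 45.0% | 45.0 |

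**3. Effect on the comparison.** Suppose t = 70% in both models, u = 0 in model 1 and u = 25% in model 2. The survey shows 70% against 70%, a difference of 0. Among all otherwise eligible positives it is 70% against 52.5%, a difference of 17.5 points.

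**4. Whether simple register totals would fill the gap.** Not reliably. The Design section allows facilities to go on offering VIA, so VIA counts can include women never HPV-tested. Model 2 laboratories test both clinic and community samples. Positives minus VIA visits is therefore not the number of undelivered results. The steps have to be linked by sample and split by place of collection.

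**5. Late samples.** The survey is done in months 13–15 of an 18-month implementation phase, and register collection is described for that phase. If community sampling continues evenly to month 18, samples from the last three months (3/18, one-sixth) fall after the survey, and those from the last weeks may have no complete follow-up in the registers either.

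**The case against.** The strongest reply is that the article does provide ways to notice the problem. Mentors visit weekly and collect clinic and HSA registers monthly for adherence. Providers and HSAs discuss barriers in focus groups at four time points. Stakeholder meetings follow each assessment round. This stands. A reader might infer that undelivered results are tracked by nothing, or that the registers serve costing alone, and the text supports neither reading. What remains is that none of these routes is assigned to produce a count: the adherence passage names the clinic and HSA registers but not the laboratory's, and focus groups and meetings yield perceptions.

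The article also condenses a fuller protocol, and Fig. 2 is not reproduced. Register fields, tracing steps and time limits may be set out there, so their absence here is no finding. Nor is the questionnaire shown. It may well ask whether a result was received, which would count screened women without a result, but not how many of them were positive.

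A reader might also turn the pilot's non-contact rate into a number of uninformed women in this trial. The article does not support that. It gives no HPV prevalence for these catchments, and the pilot figure concerns telephone delivery to 73 women, whereas model 2 returns results in person.

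Finally, one might want the study to give facilities lists of unresolved positives. That would alter follow-up mainly in one arm, and so change the feasibility being measured. It is a trade-off and not a correction.

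**Conclusion.** The point holds as one of measurement. The article promises insight into follow-up after community screening, but its one follow-up outcome is conditional on having passed the step most likely to fail in model 2. The register data that could show the step are given no outcome or analysis for it. As written, the survey outcome would overstate linkage and treatment in model 2.

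The size depends on the share never told. Over the assumed ranges the overstatement is 4.3 to 45 points, and even 10% undelivered gives 4.3 to 9.0 points. The calculation assumes that women never told would have been eligible as often as those told, and that few results go undelivered in model 1. The direction needs only that undelivered results are commoner in model 2.

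The change should be made because a better measure is available from data already planned. The finding does not say that the trial lacks oversight of these women or that tracing procedures do not exist.

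**What to change.** 1. In Table 2 and the Analysis plan, list the clinic, HSA and lab register data under Objectives 1 and 2 as the source for loss to follow-up, keeping their use in costing and adherence.
2. Make sure that the new lab and community screening registers carry a common sample code and a result-given date, if they do not already, and that VIA and treatment entries can be matched to that code.
3. Report per facility and model, with clinic- and community-collected samples separate: numbers sampled, tested, HPV-positive, positive with result given, attended VIA, and treated, with the time between steps. State that the survey ablation proportion covers only women known to be eligible.
4. Continue the register pull briefly after month 18, so that late samples have time to complete the pathway.

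The cost is modest: one or two register fields, a table from data already pulled monthly, and a few extra pulls. The linkage code should be checked against the consent waiver, which Ethical considerations grants because no identifiable data are collected. How unresolved positives are contacted and managed is for the investigators and the Ministry of Health to decide.
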